### Interim analyses {21b}

Interim analysis of study (S) AEs will be conducted at the end of year 2. The difference between the proportion of events (the test statistic) in the intervention and the expected rate of (S) AEs associated with each contraceptive method (from the published literature) will be quantified with *p*-values constructed for alpha = 0.05, two-sided. If the test statistic exceeds the boundary, then the study could be considered for early termination. In the event of any adverse or life-threatening events occurring at an unacceptable level, the PI will take appropriate action to halt the study, release a participant from the study, or modify the study procedures to reduce or eliminate the identified risk. Should a situation arise of insufficient power due to poor recruitment or early detection of (S) AEs, the investigators will discuss halting the study, when and if needed, and would report such action to the Emory and Rwandan IRB, the Data and Monitoring Safety Board (DSMB), and the NIH project officer. Completion rates of intervention activities will be monitored in a parallel fashion.

### Methods for additional analyses {20b}

#### Qualitative analyses

We will analyze the checklist quantitatively to identify organizational readiness and common service delivery or facility-level gaps. All in-depth interviews will be audio-recorded, transcribed, and undergo standard thematic analytic coding data analyses [26]. Thematic analysis is the process of identifying patterns within qualitative data without a particular theoretical perspective making it a flexible method. Two trained coders will independently read transcripts and create a preliminary codebook with definitions and examples of processes applicable to each code. Topics described in the interviews will be organized according to anticipated themes. A saturation grid will be used for the analysis of themes. To enhance reliability, coders will compare codebooks and additional themes that emerge will be included after consensus within the research team. Saturation of themes is achieved once insights begin to repeat themselves in the grid [27]. While no established standard for the sample size to achieve saturation exists for in-depth interviews, the number of interviews exceeds expert recommendations [28]. Thus, we assume a priori that we will reach saturation. Coding will be done in the NVivo software (QSR International).

#### Descriptive analyses

Descriptive analyses will evaluate the outcomes of PPFP uptake (by method type), follow-up attendance, side effects (by method type), and client satisfaction. We will assess the association between PPFP uptake and timing of counseling (chi-square test), presence of a male partner (chi-square test), and the number of counseling sessions received (chi-square test for trend).

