## Introduction

### Background and rationale {6a}

Uptake and sustainability of postpartum family planning (PPFP) services in Rwanda are low [1]. The Rwandan Demographic Health Survey (DHS) estimates that 51% of women have an unmet need for PPFP, which is higher than the unmet need during non-postpartum periods [2]. Long-acting reversible contraceptives (LARCs), including the copper intrauterine device (IUD) and hormonal contraceptive implant, are fundamental to PPFP programs. LARCs are highly effective and are the only reversible methods that may be safely used in the early postpartum period by breastfeeding women. As in most countries, postpartum use of long-acting reversible contraceptives (PPLARC) is low in Rwanda: among contracepting postpartum women, 8% use contraceptive implants and < 1% use the intrauterine device (IUD) [3, 4].

To address the high unmet need for PPFP and PPLARC in Rwanda, in 2017–2018, our research group worked closely with the Rwanda Ministry of Health (MOH) to develop and pilot test a theory-based, multi-level intervention targeting PPFP supply and demand in five government health facilities in Kigali, the capital. We trained government clinic providers to promote and provide PPFP methods, and we developed an educational counseling flipchart which detailed all PPFP options (PPLARC, injectables, pills, etc.) which was provided to 12,068 pregnant and postpartum women/couples in health facilities and the surrounding community. During our pilot, LARC uptake up to 6 weeks after delivery increased significantly (with 3372 PPIUD inserted representing a 2710% increase compared to the 6 months prior to our pilot, and 1252 implants inserted representing a 178% increase compared to the 6 months prior to our pilot), PPFP feasibility and acceptability were high among providers and clients, and side-effects were rare [5, 6].

While our short pilot was highly impactful in increasing PPFP uptake, much remains unknown: Is our PPFP intervention scalable without sacrificing quality? Will the inclusion of husbands, 85% of whom attend the first antenatal visit with their wives, increase PPLARC acceptability and uptake? Does the use of a Happy Client model of peer testimonial or PPFP promotions delivered by community health workers (CHW) increase intervention effectiveness? Is the intervention cost-effective? What demand creation strategies are most cost-effective? Is the intervention sustainable?

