### Trial design {8}

We will implement the intervention in 12 facilities in a clinic-randomized stepped-wedge design. The stepped-wedge design will ensure that each facility receives the intervention over time and provides its own standard of care control, limiting temporal bias. Facilities are high-volume and have similar client volume and staffing-to-patient ratios. Each clinic will be randomized using the SAS random number generator (SAS Institute v9.4, Cary, NC). The allocation ratio will be 1:1. This is a superiority trial.

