#### Effectiveness

##### Primary analyses

We will tabulate, by facility, a total number of all PPFP methods provided and the proportion of PPFP uptake among women who delivered at one of our facilities (overall and by method type). PP LARC uptake (by method type) will be evaluated using logistic regression and general estimating equation methods to account for the clinic-randomized design. The main predictor will be the intervention versus the control arm. For example, the following generalized linear mixed model will compute the adjusted odds ratio for taking up a PP implant: *Y*_*ijl*_ = *β*0 + *β*1 × (intervention_*ij*_) + *β*2 × (covariates_*ij*_) + *β*3 × (intervention_*ij*_ × covariates_*ij*_) + *β4*_*j*_ + *u*_*i*_ + *ε*, where *i* = clusters*, j* = time periods, *l* = individuals, *β*1 = fixed effect for intervention, *β*2 = fixed effects for covariates, *β*3 = fixed effects for interactions, *β*4_*j*_ = fixed effect for time, *u*_*i*_ = random effect for ICC, and *ε*_*ijl*_ = random residual. Covariates assessed as potential confounders will include facility volume, service volume-to-staffing ratio, and number of promotions received. Outcomes will be reported as adjusted odds ratios with 95% confidence intervals. We hypothesize that the intervention will significantly increase PP LARC uptake by comparing intervention versus control. We will also assess the independent effect of each promotional strategy on PP LARC uptake. Every promotion will be recorded and we will estimate the independent effect of receiving CHW counseling, video-based promotions, or Happy Client promotions (treating each strategy as an independent, dichotomous exposure of interest) on PPFP uptake using adjusted multivariate regression modeling with general estimating equations methods.

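### The chi-square tests of uptake against male-partner presence, counselling timing and session count ignore clinic and calendar period, and session count has no cut-off

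*Protocol article*

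**What the plan says.** Under Descriptive analyses, within Methods for additional analyses {20b}, the protocol article assesses the "association between PPFP uptake and timing of counseling (chi-square test"), and then "presence of a male partner (chi-square test), and the number of counseling sessions received (chi-square test for trend"). It names no clinic term, period term, covariate or rule for which sessions count. The section presents itself as descriptive: "Descriptive analyses will evaluate the outcomes of PPFP uptake (by method type").

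The design is clustered: "We will implement the intervention in 12 facilities in a clinic-randomized stepped-wedge design". Under Primary analyses, "PP LARC uptake (by method type) will be evaluated using logistic regression and general estimating equation methods to account for the clinic-randomized design", and the example model carries a "fixed effect for time" and a random clinic effect. The same section plans adjusted GEE for the "independent effect of receiving CHW counseling, video-based promotions, or Happy Client promotions". Male-partner presence and counselling timing are not on that list. The number of promotions appears there only as a candidate confounder.

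The Background lists among its open questions: "Will the inclusion of husbands, 85% of whom attend the first antenatal visit with their wives, increase PPLARC acceptability and uptake". Table 1 also lists factors associated with uptake as a measure, drawn from interviews and the logbook.

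**The concern.** Male-partner presence, timing and session count are individual-level exposures of the same kind as community health worker, video and Happy Client promotions. The protocol gives the latter an adjusted clustered model and the former a test that assumes independent women. If clinics or periods with more partner attendance, or more counselling, also have higher or lower uptake for other reasons, a pooled chi-square attributes that difference to the exposure and overstates its certainty.

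Session count raises a separate problem. A woman can be counselled from pregnancy until 14 weeks after birth (Eligibility criteria), yet an IUD can be inserted within ten minutes of placental delivery (PPFP service delivery training). Without a cut-off, the exposure can go on accumulating after the outcome has occurred.

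At stake are the quantitative answer on husbands and any dose-response statement about counselling.

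**Working it through.** The protocol states no alpha, power or sample size for these three tests, so there is no figure of its own to reproduce.

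**Inputs**
- From Sample size and Table 5: 12,714 counselled women in 12 clinics, so m = 12,714 / 12 = 1,059.5 per clinic.
- From Table 5: expected LARC uptake (3,687 + 1,399) / 12,714 = 40.0%, used here as a stand-in for uptake of any method.
- Assumed: two-sided alpha 0.05, and ICCs of 0.01 to 0.10 for uptake and 0 to 0.10 for exposure. The protocol says its power calculation allows for an ICC but gives no value.

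**Clustering, by formula**

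Design effect DE = 1 + (m − 1) × ICC(uptake) × ICC(exposure). True error of a nominal 5% test = 2 × [1 − Φ(1.96 / √DE)].

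- ICCs 0.02 and 0.02: DE = 1 + 1,058.5 × 0.0004 = 1.42; error 10%.
- ICCs 0.05 and 0.05: DE = 1 + 1,058.5 × 0.0025 = 3.65; error 30%.
- ICCs 0.05 and 0.10: DE = 1 + 1,058.5 × 0.005 = 6.29; error 43%.

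**Clustering, by simulation under the null** (4,000 runs, 12 clinics of about 1,060 women, 40% uptake, beta-distributed clinic rates, exposure prevalence 50%)

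| ICC uptake | ICC exposure | Plain chi-square | Stratified by clinic |
|---|---|---|---|
| 0.01 | 0 | 5.5% | 5.4% |
| 0.05 | 0 | 5.1% | 5.3% |
| 0.01 | 0.01 | 6.1% | 4.6% |
| 0.01 | 0.05 | 10.4% | 5.1% |
| 0.05 | 0.05 | 28.4% | 4.8% |
| 0.10 | 0.10 | 54.4% | 5.2% |

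With exposure prevalence set to 85%, the protocol's figure for husbands at the first antenatal visit, and both ICCs 0.05, the plain test rejects in 28% of runs.

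**Calendar period** (four periods assumed, no variation between clinics)
- Uptake and exposure both rise by 10 points: plain test 10%, clinic strata 10%, clinic-by-period strata 5%.
- Both rise by 20 points: plain test 73%, clinic strata 73%, clinic-by-period strata 5%.

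A clinic term alone therefore does not remove a shared time trend.

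**Session count** (500 runs, 12,714 women, no causal effect; assumed chance of a session 75% at antenatal care, 50% at delivery, 50% at infant vaccination)
- If sessions are unaffected by uptake, the trend test rejects in 4% of runs.
- If women who take up a method at delivery have no vaccination-visit session, it rejects in 87% of runs when 10% of users take up early, and in 100% when 30% or 70% do. Uptake then appears to fall between one and three sessions: 41% to 37%, 44% to 32%, and 49% to 17%.

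The second result shows what would happen if counselling stopped after uptake. It is not evidence that it does.

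**The case against.** The strongest defence is the role of these tests. They sit under a descriptive heading among the additional analyses, with no alpha, power or decision rule. The husband question is in the Background and is not named in the Objectives. The intervention contrast and the three named promotional strategies already have clustered models. This stands and limits the severity. It does not remove the point, because the tests are specified by name and produce p-values on a question the study poses.

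Three stronger readings are tempting, and the documents do not support them.

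- *The p-values are known to be wrong, and false positives are likely.* The protocol gives no ICC and no data on how partner presence, timing, session count or uptake vary by clinic or period. It describes the facilities as similar in volume and staffing, which does not settle the matter either way. If the exposure is equally common in every clinic and period, the plain test keeps its size.
- *Session count is a consequence of not having taken up a method.* Nothing says counselling stops after uptake. Women with an insertion are scheduled back at six weeks, at the first vaccination visit, and every woman in care during the intervention period is to be offered the intervention. The overlapping windows and missing cut-off make reverse causation possible, not established.
- *The husband question has no other analysis.* Interviews nine months after promotion, under Maintenance, include users, non-users and male partners and cover reasons for uptake and non-use. Chi-square is only the sole quantitative test.

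**Conclusion.** The point holds as an inconsistency in a stated method. The three tests are not valid in general for women clustered in 12 clinics over several periods, and the protocol handles comparable exposures differently. The size cannot be determined from the document. Over the assumed ICCs, the true error of a nominal 5% test runs from about 5% (no variation in exposure between clinics) through 6% (both 0.01), 10% (both 0.02) and 28% to 30% (both 0.05) to 54% (both 0.10). A shared calendar trend can add to this even without clinic variation. The session-count problem is conditional on counselling tending to stop after uptake, and no clustering adjustment would repair it. Severity is minor to moderate: the primary contrast is unaffected, but the quantitative answer on husbands and any dose-response claim would be unreliable.

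**What to change.** In Descriptive analyses, replace the three chi-square tests with the GEE or mixed logistic model of Primary analyses, restricted to intervention periods, with clinic and period terms and a small-sample correction for 12 clusters. Clinic should enter as a model term, because a working correlation alone adjusts the standard error but leaves confounding between clinics in the estimate. Alternatively, report these associations without p-values.

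For session count, include only sessions before delivery, or before uptake if that is earlier. A cut-off at uptake alone would still give non-users the longer counting window. Compare counselling timing among women still eligible at the time in question.

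Add age and parity only if they are available for non-users. The protocol takes both from government Family Planning logbooks and does not say whether women who took no method appear there. If they do not, complete-case analysis would drop the very women whose outcome is needed.

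The cost is a wording change before analysis, slightly more analysis work and wider intervals. The unique client code that the protocol uses to follow women across visits should allow sessions to be placed before or after delivery.

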#### Intervention cost-effectiveness and cost-utility

We will employ standard methods of cost analyses as recommended by the Second U.S. Panel on Cost-effectiveness in Health and Medicine to conduct an economic evaluation from the societal perspective (the health care sector costs plus the costs to the participant for participating in the program) to estimate the cost and cost-effectiveness of the intervention relative to control.

#### National Costed Implementation Plan

We will create a Costed Implementation Plan following the Family Planning 2020 Costed Implementation Plan Resource Kit (https://www.familyplanning2020.org/cip). Our team previously developed National Costed Implementation Plans for Couples’ HIV testing for Zambia and Botswana at the request of their respective MOHs, and the PPFP Costed Implementation Plan will be disseminated to the Rwandan MOH.

### Methods in analysis to handle protocol non-adherence and any statistical methods to handle missing data {20c}

#### Missing data

Given the uncertainty associated with imputing data, primary analyses will be complete case analyses (i.e., missing data will not be replaced). Sensitivity analyses using multiple imputation will evaluate the impact of missing data on results using the fully conditional method in SAS.

#### Crossover effects

The potential for crossover is possible if the nursing staff are redistributed during the study. The MOH will limit redistribution in study facilities during the intervention to only what is necessary (e.g., due to staff shortages). Additionally, it is possible that women could receive promotions in an intervention study facility and then deliver in a control study facility where they request PPFP. We will attempt to limit such events by encouraging women to consistently receive ANC, L&D, and IV services at the same clinic (generally beneficial to women since medical records are not easily linked across facilities). Transfers between intervention and control facilities will be recorded to quantify the potential effect of crossover.

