**Discussion:**

Adaptability and sustainability within government facilities are critical aspects of our proposal, and the MOH and other local stakeholders will be engaged from the outset. We expect to deliver PPFP counseling to over 21,000 women/couples during the project period. We hypothesize that the intervention will significantly increase the number of stakeholders engaged, PPFP providers and promoters trained, couples/clients receiving information about PPFP, and PPLARC uptake comparing intervention versus standard of care. We expect PPFP client satisfaction will be high. Finally, we also hypothesize that the intervention will be cost-saving relative to the standard of care. This intervention could dramatically reduce unintended pregnancy and abortion, as well as improve maternal and newborn health. Our PPFP implementation model is designed to be replicable and expandable to other countries in the region which similarly have a high unmet need for PPFP.

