#### PPFP service delivery training

The 5 pilot facilities (which are not randomized) will serve as sites to train and mentor nurses and midwives working in L&D and family planning at the 12 intervention facilities. The training will include a 2-day didactic session covering PPFP provision, follow-up, and use of the PPFP counseling flipchart to promote all PPFP method options (PPLARC, injectables, pills, etc.); mock counseling sessions; and PPIUD and PP implant insertion and removal trainings. Pre/post-training tests will consist of 10 true/false questions. Re-training will be offered after 1 week for trainees who fail to score > 80% on the post-training evaluation. After passing the didactic training, nurses and midwives who will be charged with insertions will be required to correctly insert 5 PPIUDs and 5 PP implants under supervision to be PPFP certified. The PPIUD insertions must include at least one of each of the following timings (which require different insertion techniques): immediate post-placental (within 10 min of placental delivery), 10 min to 48 h postpartum, and 4–14 weeks post-delivery.

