### Sample size {14}

Table 4 shows the expected number of participants included in each study activity. We assume that the proposed sample sizes shown below for in-depth interviews will allow us to reach saturation. Based on facility volume and preliminary findings, we conservatively expect to deliver PPFP promotions to 12,714 in the 12 intervention facilities (18% of reproductive age women in the catchment area) and 21,383 women/couples total across the 17 facilities (12 intervention plus 5 training facilities).

**Table 4 Tab4:** Expected number of participants included for each study activity

Specific aim	Activity	Total participants
Aim 1	In-depth interviews	12 facility directors 24 nurses in-charge of L&D and family planning 24 CHWs 5 MOH stakeholders
Aim 2	Intervention trainings	98 government facility PPFP promoters 68 community health worker promoters 78 government facility PPFP providers (70 certified) 36 Happy Client promoters
	Intervention recipients	We expect to deliver PPFP promotions to *n* = 12,714 women/couples
	In-depth interviews	25 women/couples 25 providers 25 stakeholders

We assume based on our pilot that promotions will reach 75% of pregnant women in health centers. Also extrapolating from our pilot data, we also expect to insert 3687 PPIUDs and 1399 PP implants in the 12 intervention facilities (6201 PPIUDs and 2352 PP implants total across the 17 facilities) (Table 5). Given the facility volume and previous experience, PPFP service delivery to this number of women is highly feasible. Sample size and power calculations account for intra-cluster correlation (ICC) which considers the between-cluster correlation, within-cluster correlation, and repeated measures. We assume pooled between- and within-cluster ICCs and a homogeneous intervention effect over time. We have > 80% power to detect all differences in the expected proportions shown in Table 5 comparing PPFP intervention to control.

**Table 5 Tab5:** Expected deliverables during the study time period, *n* = 12 intervention facilities. Power to detect the differences between standard of care control and intervention: > 80%

Stakeholders	Control^**a**^			PPFP intervention		
	***N*** events	Denominator	Expected %	***N*** events	Denominator	Expected %^**b**^
Clinic directors engaged	2	12	17%	12	12	100%

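### The crossover rule records only transfers between intervention and control facilities, so as written it leaves out moves to and from the five non-randomised training sites

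*Protocol article*

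**What the plan says.** The Crossover effects section names two routes. One is redistribution of nursing staff. The other concerns clients: "women could receive promotions in an intervention study facility and then deliver in a control study facility where they request PPFP". It then gives one recording rule: "Transfers between intervention and control facilities will be recorded to quantify the potential effect of crossover". The training sites do not appear in that section.

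Elsewhere the protocol treats them as a separate group. Under PPFP service delivery training: "The 5 pilot facilities (which are not randomized) will serve as sites to train and mentor nurses and midwives". Under Sample size: "we conservatively expect to deliver PPFP promotions to 12,714 in the 12 intervention facilities", set against "21,383 women/couples total across the 17 facilities (12 intervention plus 5 training facilities". Expected insertions are split in the same way: "3687 PPIUDs and 1399 PP implants in the 12 intervention facilities" against "6201 PPIUDs and 2352 PP implants total across the 17 facilities". The only timing given for the larger total is in the abstract: "We expect to deliver PPFP counseling to over 21,000 women/couples during the project period".

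Two other provisions bear on the point. Data management describes a unique code that follows clients from the community through antenatal care, delivery and infant vaccination. The primary effectiveness analysis says that every promotion is recorded, and it assesses uptake among women who delivered at a study facility.

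**The concern.** In a stepped-wedge trial each clinic supplies its own control data, so exposure of women counted in control periods bears directly on the contrast. The training sites are a third source of the intervention. They are neither waiting clinics nor clinics that have crossed over, and a rule written for intervention-control pairs does not reach them.

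Two kinds of movement matter:

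- **Exposure.** A woman promoted at a training site who delivers at a clinic in its control period would be analysed as an unexposed control. Any LARC uptake that results pulls the comparison toward no effect, and the planned crossover count would not show it.
- **Outcome.** PPIUD insertion can take place weeks after delivery, so the delivery site and the insertion site can differ. LARC obtained at a training site by a woman who delivered at a trial clinic could be missed. If it is missed in intervention periods, the effect is understated. If it is missed in control periods, the effect is overstated.

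Movement between sites is plausible. Fifteen of the 17 facilities are health centers that refer deliveries to adjoining hospitals, although the protocol does not say which hospitals are linked to which sites. The number of promotions received is a candidate covariate, and each promotional strategy is analysed as an exposure, so both would be misclassified for the same women.

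**Working it through.** **Inputs** (Sample size section and Table 5)

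- Promotions: 12,714 in the 12 clinics; 21,383 in all 17 facilities.
- PPIUDs: 3,687 and 6,201. Implants: 1,399 and 2,352.
- Table 5, control: 20 PPIUDs and 14 implants among 268 promoted women.
- Table 5, intervention: 3,687 PPIUDs and 1,399 implants among 12,714 promoted women.

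**Step 1: the plan's own figure.** The crossover rule carries no number. Table 5's reach figure reproduces: 12,714/17,870 = 71.1%, printed as 71%.

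**Step 2: volume expected at the training sites.**

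- Promotions: 21,383 − 12,714 = 8,669, and 8,669/21,383 = 40.5%.
- PPIUDs: 6,201 − 3,687 = 2,514, and 2,514/6,201 = 40.5%.
- Implants: 2,352 − 1,399 = 953, and 953/2,352 = 40.5%.

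The training sites are 5 of 17 facilities (29%). They average 8,669/5 ≈ 1,734 promotions each, against 12,714/12 ≈ 1,060 per trial clinic.

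**Step 3: what dilution could look like.** The documents give no transfer rate. Let c be the assumed share of control-period women who were exposed at a training site and take up the method at the intervention rate:

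p_c = p0 + c × (p1 − p0)

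OR = [p1/(1 − p1)] / [p_c/(1 − p_c)]

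For PPIUD, p0 = 20/268 = 7.5% and p1 = 3,687/12,714 = 29.0%. For implants, p0 = 14/268 = 5.2% and p1 = 1,399/12,714 = 11.0%. Table 5 prints 10% for the last figure; the counts are used here.

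| c (assumed) | PPIUD control | PPIUD OR | Implant control | Implant OR |
|---|---|---|---|---|
| 0 | 7.5% | 5.06 | 5.2% | 2.24 |
| 5% | 8.5% | 4.37 | 5.5% | 2.12 |
| 10% | 9.6% | 3.84 | 5.8% | 2.01 |
| 20% | 11.8% | 3.06 | 6.4% | 1.81 |

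These are crude odds ratios on Table 5's denominators (promoted women), without clustering or time effects. They show direction and rough scale only.

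**Step 4: is the PPIUD column realistic?** The Study setting section says that no providers are trained to insert PPIUDs, and Table 5 has 0 of 162 providers certified under control. Table 5 also lists 20 control PPIUDs, so capacity is very low rather than nil. A woman promoted at a training site who then delivers at a control clinic would often be unable to get a PPIUD there, so the PPIUD column probably overstates the dilution.

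**The case against.** The strongest reply is that the movement may be captured after all. A unique code follows clients across services, every promotion is recorded, and promotions and insertions are forecast for all 17 facilities. In the pilot the code tracked more than 95% of women with multiple visits. The term intervention facility could also be read loosely to cover any site delivering the programme. And this is a condensed article, so details of a transfer log may sit in a manual or analysis plan that is not shown.

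Part of this stands. It would be wrong to say that such movement is not captured; the accurate statement is that the protocol does not say it is. But the article does not merely leave the matter open. It states a rule, and the rule is too narrow on the article's own definitions, which keep the 12 clinics and the 5 training sites apart. The same section remarks that records are hard to link across facilities, so linkage cannot be taken for granted. Encouraging women to stay with one clinic reduces movement but does not measure it.

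A reader might infer more than the documents support:

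- **That the training sites promote throughout the rollout, or are the only active programme before the first step.** No dates are given, the stepped-wedge schedule is not shown, and the Study setting section describes the facilities as having no formal PPFP initiatives at present. Supervised insertions are needed for certification, which makes some early activity at these sites likely, but that remains an inference.
- **That 40.5% measures crossover.** It is a share of volume and says nothing about how many women move.
- **That the odds ratio collapses.** Setting the 34 control LARC insertions (20 + 14) and the 5,086 planned ones (3,687 + 1,399) each against 17,870 deliveries gives an odds ratio near 209. If 5% of training-site women then delivered at control clinics and took up LARC at 40% (5,086/12,714), it would fall to about 34. But Table 5 sets the 34 against 268 promoted women, and 40% uptake is implausible where PPIUD capacity is so low.

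**Conclusion.** The point holds in a limited form. The stated recording rule omits a group of sites that the protocol itself separates from the trial clinics, places in the same city, and expects to deliver 8,669 of 21,383 promotions. Followed as written, it would understate crossover, and it could misplace exposure or uptake for women who move.

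The size of any bias is unknown. Under the assumption that 5% to 20% of control women are exposed and respond as in the intervention condition, the PPIUD odds ratio falls from about 5.1 to between 4.4 and 3.1, and the implant odds ratio from 2.24 to between 2.12 and 1.81. The PPIUD figures are likely to be upper limits on dilution at each assumed share. Missed uptake among women who delivered at trial clinics could act in either direction and cannot be sized from the documents.

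None of this shows that the trial's conclusion or its power is threatened. No ICC value is printed, so the stated power cannot be recomputed. The reason to act is that the planned crossover figure would look more reassuring than it should, and the remedy is cheap.

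**What to change.** Reword the recording rule in the Crossover effects section so that it covers all 17 facilities, and carry the change into the analysis plan:

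1. Match the existing unique code against the training sites' PPFP logbooks and record moves in both directions between those sites and the 12 clinics, with dates, so that each move can be placed in a control or intervention period.
2. For women who delivered at one of the 12 clinics, count LARC obtained at a training site as uptake, in control and intervention periods alike.
3. Keep the primary analysis by randomised period, whatever promotion a woman received elsewhere.
4. Add a sensitivity analysis that excludes control-period women with a recorded training-site promotion. It should remain a sensitivity analysis, because it selects women on exposure.
5. Report the number and share of such moves by clinic and period, which supplies the transfer rate now missing.

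The cost is protocol and analysis-plan wording plus some extra linkage work. Matching across facilities will be imperfect, so the match rate should be reported with the result.
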